## **PROTOCOL**

### **Subject Recruitment**

According to the enrollment schedule, subjects recruited during project year 1 will be followed through project year 3; those recruited during year 2 will be followed through year 4; those recruited during year 3 will be followed through year 5. Over the 5-year study period, we will need to retain 50 subjects to achieve the effect size of 0.80. To reach the desired effect size, we will screen by phone approximately 250 subjects (83 subjects per year). We anticipate that 102 subjects will meet preliminary inclusion criteria and will be scheduled for the initial visit (34 subjects per year) and we expect to randomize approximately 71 subjects who meet full inclusion criteria (24 subjects per year), bearing in mind expected rate for the telephone screening (60%), failure to meet inclusion criteria at initial visit (30%) and attrition due to withdrawal from the study either by the PI or by the subject herself (30%). We estimate a 70% rate of subject inclusion in the current proposal based on: a) growing concern on the side of physicians and women alike of the utility of long-term estrogen use in postmenopause; b) interest in definition of the risk for cognitive decline among postmenopausal women and c), brain imaging procedures (in her previous studies, the PI had encountered sustained interest in participation in the studies involving PET imaging to predict possible AD).

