### **Subject Participation**

In the present study, participants will be randomly assigned to continue or discontinue their existing estrogen hormone therapy (HT) for the duration of the 2-year study. The assessment schedule includes: a) screening and identification of subjects who meet inclusion criteria; b) clinical evaluation and blood drawing for general chemistry and other analyses; c) baseline neuroimaging (MRI, PET) and neuropsychological assessments; d) interim assessments; and e) two-year follow-up assessments. All tests performed at baseline will be repeated at a 2-year follow-up. Interim assessments with subjects in between in-person visits will include telephone contact at least every other month. At each three-month interval subjects will be asked to return for a follow-up visit to evaluate their general well-being, overall functioning, and subjective memory performance. Subjects will also be encouraged to contact the research team as needed.

Psychiatric examination. The baseline psychiatric assessment includes a psychosocial history, Structured Clinical Interview for DSM-IV--Patient Edition (SCID), and mental status examination,

and will take approximately hours to complete. [name] will oversee the clinicians that perform the psychiatric assessments and evaluate interrater reliability.

The following standardized rating scales and questionnaire will be used:

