## **Data Analysis**

PET data will be analyzed by the statistical parametric mapping method of Friston and colleagues [11] to assess the main hypothesis of differences in HT randomization groups. Briefly, images from all subjects will be co-registered and reoriented into a standardized coordinate system using the SPM8 software package courteously provided by the Wellcome Department of Cognitive Neurology, Functional Imaging Laboratory (London). Data will be spatially smoothed, and normalized to mean global activity as previously described [12], except that an 8mm smoothing filter will be applied to images prior to statistical analysis. The set of pooled data will then be assessed with the t-statistic on a voxel-by-voxel basis, to identify the profile of voxels that significantly differed between subject groups. Brain regions considered appropriate for examination a priori, based upon well-established metabolic involvement in the earliest stages of prodromal Alzheimer's disease, are the bilateral precuneus/posterior cingulate areas, parietotemporal cortex in the vicinity of the angular and marginal gyri; medial prefrontal cortex, given its aging-related metabolic decline; and the medial temporal including the hippocampal area, inferior lateral temporal, and dorsolateral prefrontal cortex, for their roles in cognitive processes vulnerable to early decline in aging individuals [13, 14]. To statistically protect against multiple comparisons across the volume of the brain, a Bonferroni-type correction will be applied to twelve (left and right) regions specified by the a priori hypotheses, and group difference in those regions were noted if  $p < 0.05$  after correction; differences in other regions will be described here when  $p < 0.0005$  before adjustment. A number of analyses will be completed after stratifying the subjects according to estrogen HT formulation and various clinical variables, such as presence of APOE-4.

Clinical, demographic, and neuropsychological data will be analyzed using SPSS software version 13.0 (SPSS Inc., Chicago, IL). Two-group t-tests and chi-square tests will be used to assess any potential differences in clinical or demographic variables in the two subject groups (HT continuation or HT discontinuation). Paired t-tests will be used to assess changes in neuropsychological test performance between HT randomization groups to allow for consideration of correspondence with regional cerebral metabolism changes. Significance for

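### The sample size of 50 for an effect size of 0.80 does not match the twelve-region corrected test of the main PET hypothesis: at that threshold power per region is about 44%

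*Protocol*

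**What the plan says.** The sizing statement is in the protocol, Subject Recruitment: "Over the 5-year study period, we will need to retain 50 subjects to achieve the effect size of 0.80". The same paragraph allows 30% attrition from about 71 randomised women. It does not state alpha, sidedness, power or allocation ratio, and it does not say which outcome the 0.80 refers to.

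The protocol, Data Analysis, says that the PET data serve "to assess the main hypothesis of differences in HT randomization groups". The images are to be "assessed with the t-statistic on a voxel-by-voxel basis, to identify the profile of voxels that significantly differed between subject groups". For multiplicity, "a Bonferroni-type correction will be applied to twelve (left and right) regions specified by the a priori hypotheses", and a group difference in one of those regions counts if p is below 0.05 after correction. Only the clinical, demographic and neuropsychological comparisons are run at 0.05 without correction, and the protocol describes those as exploratory.

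The design has two arms (protocol, Subject Participation): "participants will be randomly assigned to continue or discontinue their existing estrogen hormone therapy (HT").

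**The concern.** The only main hypothesis that the protocol names is decided at a corrected threshold, yet the sizing sentence gives a number that belongs to an uncorrected one. A reader would take it that the trial can reliably detect a difference of 0.80 in its main analysis. Under the stated decision rule and an unadjusted comparison, a given region that truly differs by 0.80 would more often be missed than found. This bears on how a non-significant region is interpreted, because the protocol's conclusions are drawn region by region.

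**Working it through.** **Inputs from the protocol.** Retained N = 50 and d = 0.80 (Subject Recruitment); two-group t-statistic, twelve regions, 0.05 after correction (Data Analysis).

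**Assumptions.** Equal allocation (25 + 25), which is the split most favourable to power; 80% target power; two-sided unless noted; d in SDs of the quantity compared; a regional t-test standing in for the voxel-wise test.

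**1. Reproducing the 50.** Normal formula, n per arm = 2(z₀.₉₇₅ + z₀.₈₀)²/d² = 2(1.960 + 0.842)²/0.64 = 24.5, so 25 per arm and 50 in total. The exact t calculation gives 26 per arm (52). Attrition is consistent with this: 71 × 0.70 = 49.7. Of the uncorrected 0.05 variants tried, only two-sided with 80% power returns 50 exactly by the normal formula. One-sided with 85% power comes close (48 by the t calculation).

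**2. Power at 25 per arm, d = 0.80.** Noncentral t with df = 48 and noncentrality 0.80 × √(25/2) = 2.83.

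| Threshold | Critical t | Power |
|---|---|---|
| 0.05, two-sided | 2.01 | 79.1% |
| 0.05/12 = 0.00417, two-sided | 3.01 | 43.8% |
| 0.05/12, one-sided | 2.75 | 53.5% |

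The normal approximation gives 48.5% for the two-sided corrected case. Correcting for six bilateral areas instead of twelve regions gives 53.5% two-sided.

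**3. Detectable difference with 80% power, two-sided.** d = 0.81 at 0.05 and d = 1.10 at 0.05/12 (1.05 by the normal approximation).

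**4. Size that would keep d = 0.80 at 80% power per region, two-sided 0.05/12.** 46 per arm, or 92 retained (86 by the normal formula). This shows the size of the gap and is not a recommendation.

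**5. At least one significant region.** By simulation with equally correlated regions, power is about 80% to 95% if all twelve regions differ by 0.80 (correlation 0.7 down to 0.3), but about 43% to 63% if only one or two do. The protocol gives neither the correlation nor the expected number of affected regions.

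**6. Baseline adjustment.** If d = 0.80 is in SDs of raw uptake, an analysis adjusted for baseline works with d/√(1 − r²), df = 47. At 0.05/12 two-sided:

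| Assumed r, baseline to year 2 | Adjusted d | Power per region |
|---|---|---|
| 0.5 | 0.92 | 60% |
| 0.7 | 1.12 | 82% |
| 0.8 | 1.33 | 95% |

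None of these correlations is in the protocol. If the 0.80 is already in SDs of change, the 44% from step 2 applies to a test of change.

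**The case against.** The arithmetic is not in dispute. What can be disputed is how much it proves, and four points carry weight.

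- **Unstated inputs.** Because alpha, sidedness, power, allocation and outcome are missing, a reader might infer that the authors overlooked their own correction, or that the 50 can only have come from a single two-sided 0.05 test. The protocol does not establish either. The 0.80 might even have been set for the neuropsychological tests, which are uncorrected. That would not rescue the statement, since the main hypothesis would then have no sizing at all.
- **Longitudinal design.** Baseline tests are repeated at two years, so a reader who infers that 50 women cannot detect 0.80 in any corrected analysis goes too far. A baseline-adjusted analysis might do so if the correlation is high. Against that, the Data Analysis section describes a group t-statistic and names no adjusted model, so the higher power cannot be credited to the plan as written.
- **Per-region versus any-region.** It is tempting to read 44% as the chance that the whole trial succeeds. It is not. A difference in any one region could support the main hypothesis, and that chance is much higher if the effect is widespread. Per-region power still matters because results are reported by region.
- **Approximation.** The planned test is voxel-wise, and the exact form of the Bonferroni-type correction is not given. Searching within regions could make the threshold stricter, while peak-voxel effects could exceed a regional mean. A step-down version such as Holm starts at the same 0.05/12.

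These points limit the claim without removing it: no corrected variant of the unadjusted test that was tried reaches 80% at N = 50 and d = 0.80.

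**Conclusion.** The concern holds in a limited form. The stated size and the stated decision rule do not agree. With 25 per arm and an unadjusted regional t-test, d = 0.80 has 79% power at an uncorrected two-sided 0.05, but about 44% per region (53% one-sided) at 0.05/12. There the detectable difference is about 1.10 rather than 0.80. This rests on equal allocation, on 80% as the target power for the detectable difference, on the 0.80 referring to the PET comparison, and on the regional test as a proxy for the voxel-wise one. It does not show that the trial as a whole has 44% power, or that more women must be recruited.

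**What to change.** Restate the sizing sentence in Subject Recruitment so that it describes the planned analysis, for example:

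> *50 completers (25 per arm) give 80% power, two-sided, for d of about 1.10 in a single a priori region after correction for twelve regions; d = 0.80 has about 79% power only at an uncorrected 0.05.*

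Add the allocation ratio, the outcome to which the effect size refers, and whether it is in SDs of follow-up uptake or of change. If the sponsor wants to quote a higher power from a baseline-adjusted PET analysis, that model must be specified in the protocol and the baseline to year-2 correlation supplied with its source. The 60%, 82% and 95% above are illustrations and should not be copied into the text.

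The cost is one rewritten sentence with a less favourable figure. It needs no extra patients and no change to study conduct. Unless the adjusted model is adopted, the analysis does not change either.

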### *Inclusion and Exclusion Criteria*

The proposed study design calls for identifying subjects at risk for cognitive decline but not necessarily for developing dementia during a two-year period. Thus, estimates for incipient dementia are not critical for the study design, since incipient dementia is not a primary outcome measure. For the proposed study, we will use the following inclusion criteria:

1. Willingness to sign the Human Subject Protection Consent Form prior to enrollment into the study.
2. Willingness to be randomized to continuation/discontinuation of estrogen replacement therapy.
3. Women 50-65 years of age.
4. One year or more post complete cessation of menses.
5. Current estrogen use for at least one year.
6. Adequate visual and auditory acuity to allow neuropsychological testing.
7. Greater than 8 years of educational achievement to allow adequate neuropsychological testing.
8. Willingness to undergo brain imaging procedures (MRI and PET).
9. Risk for cognitive decline, as defined by one or more of the following:
  - Personal history of mood disorder.
  - Family history of AD.
  - APOE-ε4 allele.

Because cognitive decline may be caused by various conditions, it is critical to exclude subjects with impairment from numerous causes (e.g., vascular disease, etc.). In addition to the above inclusion criteria, we will use the following exclusion criteria:

1. Diagnosis of possible or probable AD [1] or any other dementia (e.g., vascular, Lewy body, frontotemporal).

2. Evidence of neurologic or other physical illness that could produce cognitive deterioration. Volunteers with a history of TIAs, carotid bruits, or lacunes on MRI scan will be excluded. During physical and neurological examination, subjects will be screened for Parkinson disease using the motor examination (items 18-31) of the Unified Parkinson's Disease Rating Scale [2], an instrument with high inter-observer concordance, to quantify presence and degree of symptoms.
3. History of myocardial infarction within the previous year or unstable cardiac disease.
4. Significant cerebrovascular disease, as evidenced by neurological examination, uncontrolled hypertension (systolic BP > 170 or diastolic BP > 100), history of significant liver disease, clinically significant pulmonary disease, diabetes, or cancer.
5. Because medications can affect cognitive functioning, need for a drug that may significantly affect psychometric test results will be reason for exclusion. Use of any of the following drugs will also exclude subjects: centrally active beta-blockers, narcotics, clonidine, anti-Parkinsonian medications, antipsychotics, benzodiazepines, systemic corticosteroids, medications with significant cholinergic or anticholinergic effects, anti-convulsants, warfarin, or sporadic use of phytoestrogen-containing products\*.
6. Evidence of depression as determined by a HAMD (Hamilton, 1960) score of 8 or more (17-item version).
7. History of drug or alcohol abuse.
8. Contraindication for MRI scan (e.g., metal in body, claustrophobia).
9. Current episode of mental illness (including mood disorders), or past history of mental illness (excluding mood disorders).
10. Cognitive decline, as evidenced by change in daily functions and/or MMSE <24 (Folstein et al, 1975).

\*Because phytoestrogen-containing products can produce estrogen-like agonist and antagonist effects [3, 4], all subjects will be asked not to start use of phytoestrogen-containing products (i.e. soy, tofu, herbs, topical preparations, etc.) during study participation. Similarly, all subjects will be asked not to start use of preparations with putative mood or cognitive enhancing properties (i.e., St. John's Wort, ginko biloba, etc.). We will enroll subjects taking these agents if they have been taking them at a stable dose for at least two months. We will request those women who are already using phytoestrogen-containing products and/or mood/cognition-affecting preparations to continue taking those supplements and to maintain a consistent dosage.

### **Subject Participation**

In the present study, participants will be randomly assigned to continue or discontinue their existing estrogen hormone therapy (HT) for the duration of the 2-year study. The assessment schedule includes: a) screening and identification of subjects who meet inclusion criteria; b) clinical evaluation and blood drawing for general chemistry and other analyses; c) baseline neuroimaging (MRI, PET) and neuropsychological assessments; d) interim assessments; and e) two-year follow-up assessments. All tests performed at baseline will be repeated at a 2-year follow-up. Interim assessments with subjects in between in-person visits will include telephone contact at least every other month. At each three-month interval subjects will be asked to return for a follow-up visit to evaluate their general well-being, overall functioning, and subjective memory performance. Subjects will also be encouraged to contact the research team as needed.

Psychiatric examination. The baseline psychiatric assessment includes a psychosocial history, Structured Clinical Interview for DSM-IV--Patient Edition (SCID), and mental status examination,

and will take approximately hours to complete. [name] will oversee the clinicians that perform the psychiatric assessments and evaluate interrater reliability.

The following standardized rating scales and questionnaire will be used:

(1) Structured Clinical Interview for DSM-IV Axis I disorders-Patient Edition (SCID-I/P) [5] is a structured interview that allows for making diagnoses in accordance with DSM IV. The interview takes approximately two hours depending on the pathology of the subject, and can, if necessary, be administered over several sessions. The SCID has screening and skip-out questions that allow for rapid assessment of Axis I diagnoses. The SCID will be administered in its entirety at the initial visit. This will be used to establish presence of any psychiatric diagnoses, current or in remission. (2) Mini-Mental State Examination [6] - a score of 24 or more is needed for a diagnosis of AAMI, 23 or less for AD; (3) Clinical Global Impression Scale (CGI Improvement and Severity Subscales) - used to measure global severity and change from the baseline state of behavior; (4) Hamilton Rating Scale for Depression (17-item version [7]) is an observer rated scale with items assessing symptoms of major depression. The scale has been well validated in the depressed population, and takes a ½ hour to administer. The scale will be administered at the screening visit and every 6 months thereafter. A score above 8 indicates depression, subjects with scores greater than 8 will be excluded from the study.

Physical/neurological examination. Given the numerous physical conditions that may cause cognitive impairment [8], comprehensive physical and neurological examinations will be performed on each patient. The standardized neurological examination yields a quantitative measure of neurological status (developed by [name], Director of the UCLA AD Research Center). In addition, outside medical records are routinely reviewed. We also include a brief handedness questionnaire (see Appendix) and the Unified Parkinson's Disease Rating Scale [2].

Neuropsychological assessment. The neuropsychological test battery includes two components: (1) baseline memory tests; (2) and follow-up measures to assess cognitive decline. The baseline battery includes measures that we expect to be sensitive to subtle changes in cognitive function as well as instruments that appear to have some value in prospectively identifying individuals who eventually decline and develop dementia. These tests are included under the assumption that cognitive changes may emerge in the same functional areas that are affected in the earliest stages of clinically detectable AD. The tests will be given during afternoon sessions to avoid diurnal effects. The neuropsychological test battery will include measures of secondary memory, retrieval from semantic memory/language, visuospatial ability, and frontal functions. The tests were chosen based on prior studies that indicate their ability to predict cognitive decline [9] and sensitivity to predict cognitive change [10]. Tests in the battery will include the Auditory Consonant Trigrams (ACT), Benton Visual Retention Test (BVRT), Boston Naming Test (BNT), Color Trail Making Test (Color Trails 1 & 2), Delis Kaplan Executive Function System (DKEFS) - Color-Word, and Verbal fluency subtests, Rey-Osterrieth Complex Figure Test (RCFT), Wechsler Adult Intelligence Scale-3rd Edition (WAIS-III) - Digit Span, Digit Symbol Coding, and Letter Number Sequencing subtests, and the Wechsler Memory Scale-III (WMS)-Logical Memory I & II subtests. Two subtests from the Wechsler Abbreviated Scale of Intelligence (Vocabulary and Matrix Reasoning) were used to characterize intelligence (IQ).

Laboratory Assessment. Laboratory studies are required to identify treatable medical illness that may cause cognitive impairment. We will use the laboratory screening recommended by

consensus groups for the investigation of dementia syndromes [8]: complete blood count with differential, urinalysis, screening test for syphilis, TSH, vitamin B12, drug screen, sodium, potassium, chloride, carbon dioxide, creatinine, glucose, bilirubin, calcium, cholesterol, lactic dehydrogenase, alkaline phosphatase, inorganic phosphorous, total protein, albumin, SGOT/PT, blood urea nitrogen, uric acid, triglyceride, and globulin. If a potentially treatable abnormality is identified, appropriate referral will be made. In addition, estradiol and FSH blood levels will be obtained at the screening visit to verify current estrogen use and menopausal status. Estradiol blood levels will also be obtained every 3 months to monitor compliance of randomization assignment.

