## **Risks to the Subjects**

Human Subjects Involvement and Characteristics. This project will screen approximately 250 postmenopausal female subjects, 50-65, in relatively good physical health who either, at risk for cognitive decline (personal or family history of mood disorder, hypothyroidism, family history of AD, APOE- $\epsilon 4$  allele). Exclusion criteria include: a) diagnosis of possible or probable AD, or any other dementia (e.g., vascular, Lewy body, frontotemporal), b) evidence of neurologic or other physical illness that could produce cognitive deterioration. Volunteers with a history of TIAs, carotid bruits, or lacunes on MRI scan will be excluded. During physical and neurological examination, subjects will be screened for Parkinson disease using the motor examination (items 18-31) of the Unified Parkinson's Disease Rating Scale, an instrument with high inter-observer concordance, to quantify presence and degree of symptoms, c) history of myocardial infarction within the previous year or unstable cardiac disease, d) significant cerebrovascular disease, as evidenced by neurological examination, uncontrolled hypertension (systolic BP > 170 or diastolic BP > 100), history of significant liver disease, clinically significant pulmonary disease, diabetes, or cancer, e) use of any of the following drugs will also exclude subjects: centrally active beta-blockers, narcotics, clonidine, anti-Parkinsonian medications, antipsychotics, benzodiazepines, systemic corticosteroids, medications with significant cholinergic or anticholinergic effects, anti-convulsants, warfarin, or sporadic use of phytoestrogen-containing products, f) evidence of depression as determined by a HAMD score of 8 or more (17-item version), g) history of drug or alcohol abuse, h) contraindication for MRI scan (e.g., metal in body, claustrophobia), i) current episode of mental illness (including mood disorders), or past history of mental illness (excluding mood disorders), j) cognitive decline, as evidenced by change in daily functions and/or MMSE <24.

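### The HAMD depression cut-off is stated two ways, and the version in the rating-scale section does not say whether it applies only at entry or also to scores after randomisation

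*Protocol*

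**What the plan says.** Three places in the protocol set a HAMD threshold on the 17-item scale.

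- Inclusion and Exclusion Criteria, exclusion 6: "Evidence of depression as determined by a HAMD (Hamilton, 1960) score of 8 or more (17-item version".
- Risks to the Subjects, item f: "evidence of depression as determined by a HAMD score of 8 or more (17-item version".
- Subject Participation, rating scale 4: "A score above 8 indicates depression, subjects with scores greater than 8 will be excluded from the study".

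In the third place, the sentence immediately before the rule sets the schedule: "The scale will be administered at the screening visit and every 6 months thereafter". Nothing ties the rule to the screening score.

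The design is a randomised comparison: "participants will be randomly assigned to continue or discontinue their existing estrogen hormone therapy (HT) for the duration of the 2-year study". One of the three alternative risk routes into the trial is "Personal history of mood disorder". On numbers, the Subject Recruitment section states that "we will need to retain 50 subjects to achieve the effect size of 0.80" and that "we expect to randomize approximately 71 subjects who meet full inclusion criteria", with 30% attrition that covers withdrawal by the investigator as well as by the subject.

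**The concern.** There are two separate problems.

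The first is an eligibility threshold that differs by one point between sections. Sites cannot apply both versions to a woman who scores exactly 8.

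The second is scope. Entry already requires a low HAMD and no current mood episode, so a later score above the threshold is a change since entry. If the rule is applied to the six-monthly scores, women leave because of something measured after randomisation that the assignment might influence. The main hypothesis is a PET difference between the randomised groups, and the baseline tests are repeated at two years. The protocol does not say that a woman excluded on a later HAMD score still has those tests or stays in her arm. An analysis plan could define the analysis set, but it cannot recover scans that were never done.

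**Working it through.** **Cut-offs side by side.** HAMD is a whole-number score. Exclusion 6 and item f exclude scores of 8 and above. The rating-scale text excludes scores above 8, that is 9 and above. The rules agree at every score except 8.

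**Scope, from the wording.** For the literal reading: the rule follows the repeat schedule directly, refers to exclusion from the study rather than from entry, and is the only use that text gives to the HAMD scores. For the entry-only reading: the protocol elsewhere uses exclusion for eligibility, and its one explicit on-study rule (worsened cognitive performance, under Data and Safety Monitoring) speaks of removal and names subjects in either arm. The text does not settle it.

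**The plan's own numbers.** With two-sided alpha 0.05, 80% power and 1:1 allocation (assumed, as none is stated), n per arm = 2(1.96 + 0.84)² / 0.80² = 24.5, rounded up to 25, so 50 in total. Exact t-test power with 25 per arm is 0.79. Allowing for attrition, 50 / 0.70 = 71.4, or 72 rounded up, against about 71 stated. The figures reproduce.

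**Illustration of bias.** The documents give no removal rates, no mood-outcome correlation and no effect of assignment on mood, so all three are assumed. Suppose the highest-scoring fraction q on mood is removed within an arm. With z the upper-q point of the standard normal, the mean mood of those retained falls by φ(z)/(1 − q) SD:

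| q | shift in mood (SD) |
|---|---|
| 10% | 0.195 |
| 25% | 0.424 |
| 30% | 0.497 |

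The bias in the group difference is the correlation times the difference in shifts:

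| Removed, continue v discontinue | correlation 0.3 | correlation 0.5 |
|---|---|---|
| 10% v 10% | 0 | 0 |
| 10% v 25% | 0.3 × 0.229 = 0.07 | 0.5 × 0.229 = 0.11 |
| 10% v 30% | 0.3 × 0.302 = 0.09 | 0.5 × 0.302 = 0.15 |

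If worse mood goes with worse outcome, the bias favours the arm that loses more women, here discontinuation. A milder case, 5% v 15% with correlation 0.2, gives 0.03 SD.

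**Illustration of numbers.** With 35.5 per arm, 10% v 25% removes 35.5 × 0.10 + 35.5 × 0.25 = 12.4 women. The attrition allowance is 71 × 0.30 = 21.3, so this would use 12.4 / 21.3 = 58% of it. Power falls only if such removals come on top of the 30%: at 5% in both arms 47.2 women remain (power 0.77), and at 10% v 30% 39.8 remain (power 0.68).

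**The case against.** The strongest case against is that the rating-scale sentence merely repeats the entry criterion. It sits in a list that follows a paragraph on the baseline psychiatric assessment, the neighbouring MMSE item also just describes cut-offs, and the protocol uses different words where it plainly means on-study removal. This stands to the extent that a reader might infer a definite rule for dropping randomised women who become depressed, and the documents do not support that as fact. They support an unresolved ambiguity, in which staff following the sentence literally would drop such women.

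Several other objections also hold. No passage says that stopping estrogen raises HAMD, and mood-disorder history is only one of three routes in, so how many women are susceptible is unknown. The largest bias shown, 0.15 SD, is under a fifth of the 0.80 design effect and about half the standard error with 50 retained (2/√50 = 0.28 SD). Withdrawals by the investigator are already within the 30%, so no power shortfall follows unless the removals are additional. A score that triggered exclusion would already have been recorded, so an effect on mood itself would not necessarily be hidden.

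None of this removes the one-point conflict or supplies the missing statement of scope. Leaving the analysis set to an analysis plan is normal, but whether two-year data are still collected is for the protocol.

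**Conclusion.** The cut-off conflict is certain and confined to a score of exactly 8. The scope of the rating-scale sentence is unclear; its literal reading is a post-randomisation exclusion, and an entry-only meaning remains open.

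Harm to the randomised comparison is conditional on three things: the rule is used after randomisation, women excluded under it are not followed to two years, and mood responds to the assignment so that losses differ by arm. Under the assumed 10% v 25% to 30% removal and correlations of 0.3 to 0.5, the bias is about 0.07 to 0.15 SD; with equal losses it is zero in this model. These figures show what could happen and are not estimates for this trial. A reader might also infer that the trial would be underpowered because of this rule; the documents do not show that.

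**What to change.** Reconcile exclusion 6, item f of Risks to the Subjects and the rating-scale text to one HAMD cut-off. State whether the rating-scale rule governs entry only or later scores as well. Both choices are for the sponsor.

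Whatever clinical response is chosen to a raised score after randomisation, state that the woman still has the two-year PET and neuropsychological assessments where she agrees, and is analysed in the arm to which she was randomised. Report the six-monthly HAMD by arm.

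The cost is protocol wording, plus completing the already planned two-year assessments in women who might otherwise have been dropped. HAMD is already scheduled. The small downside is that some two-year assessments will be made in women with depressive symptoms, which a sensitivity analysis can address.
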